## 4.6 MISSING DATA

Every effort will be taken to minimise missing data. If imputation (e.g., mean substitution) is part of the validated measure it will be performed, see Appendix 1 for measure scoring rules. Where there are no missing data rules for the measure, if the number of missing items on an outcome is 20% or less, then the missing value for the item will be substituted by the individual's mean score for the remaining items on the scale (Bono, Ried, Kimberlin and Vogel 2007). If there are more than 20% missing items in the scale the outcome measure will not be calculated for the participant at that time point and multiple imputation methods will be used.

In accordance with the recommendations of Jakobsen, Gluud, Wetterslev and Winkel (2017), if the proportion of missing data is less than 5%, no imputation of missing data will be performed, and analyses will be based on complete cases. If the proportion of missing data is equal to or greater than 5%, a missing completely at random test devised by Little (1998) will be performed to assess whether the data is missing completely at random (MCAR). If this test indicates that data is missing completely at

random then analyses will be based on complete cases, else independent t-tests and Chi-square tests will be conducted to investigate whether the data is missing at random (MAR). If these tests suggest that the missing data is MAR, then predictive mean matching multiple imputation methods will be employed. Otherwise, additional modelling guided by clinical knowledge would be required to simulate the missing data mechanism and impute the missing data.

For multiple imputations, the number of imputations completed will be dependent upon the percentage of missing data (White et al., 2011). The missing outcome measures will be imputed using Allocation Group and Stratification factors (Site) and other variables that are deemed to be predictors of missingness. Variables will be assessed for being predictors of missingness by running statistical tests on completers versus non completers and evaluating if any differences are present between the two.

Variables to be assessed as predictors of missingness include;

- Age
- Sex
- Ethnicity
- Education
- Disability
- Occupation
- Drugs
- CV19 (diagnosed conditions (before/during))
- Number of vaccines
- Cognition

If MI is used, complete case analysis will also be conducted as a sensitivity analysis to check the assumptions of the MI models, see section 6.8. In line with the recommendations of Jakobsen et al (2017), if more than 40% of data is missing for an outcome measure the data will not be imputed and an analysis will be conducted on complete cases, though the results of the analysis will be interpreted tentatively.

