| A 24-item questionnaire, with 19 self-rated questions and 5 rated by bed partner, to assess overall sleep quality.                                                                                                                                                                                                                                                                                                                                                                                                                                                                                                                                                                                                                                                                                                                                                                                | 
The 19 self-rated questions are combined to form seven component scores.
 
Each component is scored from 0-3 on a variety of scales.
 | 
The final score is the total of each component.
 
Original paper isn't clear on how to score some of the components ((e.g., component 3 how to categorise "6"). The measure will be scored in line with this reference: https://biolincc.nhlbi.nih.gov/media/search?q=PSQI)
 | 7 subscales (components): Subjective sleep quality, sleep latency, sleep duration, habitual sleep efficiency, sleep disturbances, use of sleep medication and daytime dysfunction. | None. | None. | A higher score indicates severe difficulties in all areas. |

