| A 10-item questionnaire to assess Post-Exertional Malaise (Pem)                                                                                                                                                                                                                                                                                                                                                              | 
Questions 1 – 5 are rated for frequency and severity: On a 5 point likert scale (0-5).
 
Questions 6-8 and 10 are rated Yes/No.
 
Question 9 rated 6 point scale.
 | 
DSQ PEM SUUBSCALE: A frequency of at least 2 and a severity of at least 2 on any one of the 5 questions indicate that PEM is present.
 
If threshold is met the DSQ PEM is "Yes;" otherwise it is "No."
 
A frequency of 2 on one question and a severity of 2 on a separate question does not satisfy the threshold.
 | 2 – Post-Exertional Malaise scale of the DSQ (Q1-5) and indicator questions (Q6-10) | 
If all items are missing then Pem not calculated , if 1 item missing then PEM can still be calculated .
 
If 1 item in a bunch missing then PEM shouldn't be calculated .
 |     | Score indicates if PEM is present or not                       |

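### SAP 4.6's default item-mean substitution covers the PSQI, where it gives invalid values for items not scored 0 to 3; the DSQ-PEM missing-item clauses are undefined and appear to conflict

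*Combined protocol and SAP*

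**What the plan says.** SAP 4.6 sets a default for item-level gaps: "Where there are no missing data rules for the measure, if the number of missing items on an outcome is 20% or less", each missing item takes the participant's "mean score for the remaining items on the scale". Beyond that limit the score is left uncalculated: "If there are more than 20% missing items in the scale the outcome measure will not be calculated for the participant at that time point". Missing scores then go through the later steps of 4.6, which lead to complete-case analysis or multiple imputation.

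SAP Appendix 2 describes the PSQI as "A 24-item questionnaire, with 19 self-rated questions and 5 rated by bed partner, to assess overall sleep quality". It adds: "The 19 self-rated questions are combined to form seven component scores", and "Each component is scored from 0-3 on a variety of scales". Its missing-value column reads None. The entry also notes that the source paper leaves unclear how a 6 should be categorised for component 3; sleep duration is third in the listed components.

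For the DSQ-PEM, Appendix 2 records post-exertional malaise (PEM) as present when any one of five questions has both frequency and severity of at least 2, and otherwise as No. Its missing-value cell says that PEM is not calculated if all items are missing and can be calculated if one is missing. It then says: "If 1 item in a bunch missing then PEM shouldn't be calculated". Neither 'item' nor 'bunch' is defined.

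SAP 4.3 treats every secondary outcome, including these two, as exploratory.

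**The concern.** A person's mean over the other items is a reasonable stand-in only when all items share one response format. The PSQI has no rule of its own and no exception is written, so a programmer who follows 4.6 would average unlike quantities and put the result in place of, say, hours of sleep. A record with 20% or less missing is then scored and never reaches the later missing-data steps. The outlier check in SAP 4.7 would not necessarily catch a wrong value that looks plausible. Because SAP 6.7 adjusts for the baseline score, the error can enter at baseline as well as at 3 and 6 months.

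The DSQ-PEM problem is different. Nothing is filled in, but two programmers could score the same incomplete record differently, and one of the readings can produce a No that the data do not support. SAP Appendix 1 analyses PEM as a binary outcome by logistic regression, so that No would be a misclassification.

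**Working it through.** The plan states no figure on this point. The sample size (88 analysed, 118 randomised) rests on the BGSI and is unaffected.

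**PSQI: how many fills are allowed.** This is the whole part of 0.20 × number of items. The SAP does not say which count applies.

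- 24 items: 0.20 × 24 = 4.8, so 4.
- 19 self-rated items: 0.20 × 19 = 3.8, so 3.
- 7 components: 0.20 × 7 = 1.4, so 1.

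**PSQI: what value is filled.** With one of 19 items missing, the fill is the sum of the other 18 divided by 18. The documents do not list item formats, so three assumptions are shown.

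- *(a) Only duration is in hours (4 to 8); the other 18 items are 0 to 3.* A missing duration is filled with the mean of 18 items scored 0 to 3, which is 0 to 3 'hours' whatever the true sleep. A missing 0-to-3 item is hardly disturbed. If the others all equal m and duration is h, the fill is (17m + h)/18, a shift of (h − m)/18. That runs from (4 − 3)/18 = 0.06 to (8 − 0)/18 = 0.44 point.
- *(b) Two clock times, latency in minutes and duration in hours are all entered raw; the other 15 items all equal 1 or all equal 2.* Over four illustrative profiles, the fill for a missing 0-to-3 item runs from (14 × 1 + 11 + 15 + 7 + 7)/18 = 3.0 to (14 × 2 + 23 + 60 + 7 + 5)/18 = 6.8, at or above the item's maximum of 3. The fill for missing hours runs from (15 × 1 + 11 + 15 + 7)/18 = 2.7 to (15 × 2 + 23 + 60 + 7)/18 = 6.7, driven by clock times and minutes.
- *(c) Substitution is done on components.* Each is 0 to 3, so a mean of the other six also lies within 0 to 3 and can be interpreted.

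Seven components of 0 to 3 give a total of 0 to 21 (7 × 3). A bad fill that feeds one component can move the total by at most 3 points. The actual change cannot be computed, because the documents do not give the component cut-points.

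**DSQ-PEM: one rating missing.** The ratings below are illustrative.

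| Pattern | What the data settle | Scored despite the gap | Not scored |
|---|---|---|---|
| Question 1 has frequency 3, severity 3; question 2 lacks severity | Yes | Yes, correct | Settled Yes lost |
| Questions 1 to 4 all have 1 and 1; question 5 has frequency 3, no severity | Nothing | No, possibly wrong | Missing, correct |
| Questions 1 to 4 all have 1 and 1; question 5 has frequency 0, no severity | No | No, correct | Settled No lost |

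Neither clause is right for all three patterns. Nothing covers more than one but not all items missing.

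**The case against.** Four points can be made on the other side.

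**PSQI scores.** A reader might infer that PSQI scores under this plan would be meaningless. The documents do not support that. Substitution at component level would be interpretable, and under assumption (a) a missing 0-to-3 item moves by less than half a point. What stands is that 4.6 is worded for items, not components, and makes no exception for mixed formats.

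**Size.** The large distortions in (b) depend on clock times and minutes being entered raw, which the documents do not say. Appendix 2 also defers PSQI scoring to an outside reference. This objection stands: only the presence of an off-scale raw value is documented.

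**DSQ-PEM clauses.** A reader might infer that they flatly contradict each other. One reading reconciles them: 'item' means a whole question and 'bunch' means its frequency and severity pair. So the conflict is apparent, not proven. That reading is still unsatisfactory, since a wholly missing question would allow scoring and a half-missing one would not, and a No could still be returned when the missing question might have met the threshold.

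**Imputation.** A reader might also infer that incomplete DSQ-PEM records are filled in and so bypass imputation. They are not. The DSQ-PEM has its own rule, so the 20% default does not govern it, and an uncalculated PEM is missing rather than misclassified.

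**Conclusion.** The point holds in a limited form and is minor. Followed as written, SAP 4.6 gives an invalid value for any missing PSQI item not scored 0 to 3. This rests on three things in the SAP: the item-level default, the absence of a PSQI rule, and the raw 6 that needs categorising. How large the error is depends on item formats that the documents do not give. The DSQ-PEM clauses are ambiguous and in apparent conflict, and scoring with a rating missing can return an unsupported No.

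The number of affected records is unknown; I assume it is small. Both outcomes are exploratory secondary outcomes. The primary outcome, the sample size and the main conclusion are untouched.

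**What to change.** **SAP 4.6.** Limit item-mean substitution to scales whose items share one response format, for example GAD-7, the Chalder scale, and SF-DEM after reverse coding. For the PSQI, score a component only from its own items. If a component cannot be scored, set the total to missing and apply the existing 4.6 steps. This also removes the question of which item count the 20% refers to.

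**Appendix 2, DSQ-PEM.** Replace the missing-item clauses with one rule:

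- Yes if any complete frequency and severity pair meets the threshold;
- No if every one of the five pairs is ruled out, meaning that at least one observed rating in the pair is below 2;
- otherwise missing.

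Requiring all five pairs to be complete before recording No would be simpler, but it would discard settled negatives such as the third pattern in the table.

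While editing, correct the pointer in 4.6: it sends the reader to Appendix 1 for scoring rules, which are in Appendix 2.

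**Cost.** A few sentences and some scoring code, and a few more missing PSQI and PEM values. These will not necessarily be imputed. SAP 4.6 uses complete cases when less than 5% is missing, when the test indicates data missing completely at random, or when more than 40% is missing. Missing PEM values will fall only on people with no observed Yes, so the report should give their number by arm.

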## 6 Statistical analysis

Primary analysis of the BGSi will be completed on an ITT basis at the 3 month endpoint using mixed effect models. Stratification variables will be incorporated into the model and other potential factors that could affect the results will be determined a priori and considered for inclusion in the models. All treatment effect estimates will be presented with 95% confidence intervals and 5% level of significance will be used. Analysis of secondary outcomes will follow the same analysis model as the primary analysis where possible. Binary outcomes will be analysed using multi-level logistic regression. Exploratory analysis will be conducted to investigate the effect of phenotypes and comorbidities on the outcome.

Where possible missing data will be minimised however a maximum-likelihood multiple imputation approach will be used with a sensitivity comparison of complete case dataset. The planned analysis will be specified in the statistical analysis plan (SAP), any deviations from the analysis plan will be justified and fully documented in the results report.

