## **4. STATISTICAL PRINCIPLES**

All those randomised will be included in the analysis based on an intention to treat (ITT) principal.

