### **4.1 SAMPLE SIZE JUSTIFICATION**

A sample of 88 (44:44) will be required to detect an effect of 0.7 on the BGSI at 3 months with 90% power at a 5% significance level. Incorporating an attrition of 25% will require recruitment and randomisation of 118 participants (59:59). Therefore, 120 participants will be recruited from the same clinics. Participants in WS1 can if desired take part in WS2.

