### **4.3 LEVELS OF CONFIDENCE AND P-VALUES**

All statistical tests will be two-sided and performed using 5% level of significance. All confidence intervals presented will be 95%, unless stated otherwise.

Secondary outcomes will not be adjusted for multiple comparisons, as standard. The primary outcome is powered for at the significance level stated. Analysis of all secondary outcomes is considered exploratory, and any statements of results related to these outcomes will be reported appropriately.

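### SAP 4.6 lets a non-significant Little's test make complete cases the primary analysis, against the protocol's imputation plan and with no sensitivity analysis on that route

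*Combined protocol and SAP*

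**What the plan says.** SAP 4.6 sets out a sequence for missing outcomes.

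- Below 5% missing: complete cases.
- At 5% or more: Little's test. If it indicates MCAR, "then analyses will be based on complete cases, else independent t-tests and Chi-square tests will be conducted", the second half being the step that is meant to establish MAR.
- If those tests suggest MAR: multiple imputation (MI) by predictive mean matching. If not: unspecified modelling guided by clinical knowledge, again ending in imputation.
- Above 40% missing: complete cases, interpreted tentatively.

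On sensitivity, SAP 4.6 says: "If MI is used, complete case analysis will also be conducted as a sensitivity analysis to check the assumptions of the MI models". SAP 6.9 repeats the condition that MI was used. Neither section adds an analysis when complete case is primary.

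Protocol section 6 has no such tests: "a maximum-likelihood multiple imputation approach will be used with a sensitivity comparison of complete case dataset". SAP section 4 states: "All those randomised will be included in the analysis based on an intention to treat (ITT) principal".

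**The concern.** A test that fails to reject is treated as evidence that its null hypothesis is true, and that result selects the primary analysis after the data are in. The next step asks tests on observed variables to establish MAR. Whether data are MAR or MNAR depends on the unseen values, so such tests can show a departure from MCAR but cannot tell MAR from MNAR.

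At stake is which participants the headline estimate rests on and whether anything checks it. At the planned attrition, the complete-case branch leaves out about 30 randomised participants. Participants in the RCT know their allocation and rate their own goals (protocol 5.2.2.3 and 7.3), so dropout linked to lack of benefit is plausible. The plan requires no defined analysis of that possibility.

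**Working it through.** **1. The plan's own figures.** SAP 4.1: "A sample of 88 (44:44) will be required to detect an effect of 0.7 on the BGSI"; the power aimed for is 90%, on the 3-month score. A two-sample t-test with d = 0.7 needs 43.87, so 44 per arm (88 in all), with power 90.1%. Allowing for 25% attrition, 88 / 0.75 = 117.3, which rounds to 118 (59:59). The figures reproduce. Expected missing: 118 − 88 = 30, or 25.4%, inside the 5–40% range.

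**2. Power of Little's test.** SAP 4.3 sets the level: "All statistical tests will be two-sided and performed using 5% level of significance". No other level is given for Little's test, so I use 5%. The SAP does not list the variables that enter the test, so I take p = 1, 5 or 10. I assume one dropout pattern and a completer–dropout difference of d SD in one variable. The statistic is then approximately non-central chi-square on p degrees of freedom, with

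λ = N·m(1−m)·d² / [1 + m(1−m)·d²], where N = 118 and m = 30/118, so m(1−m) = 0.1896.

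For d = 0.5: λ = 118 × 0.1896 × 0.25 / (1 + 0.1896 × 0.25) = 5.59 / 1.047 = 5.34.

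| Difference | λ | p = 1 | p = 5 | p = 10 |
|---|---|---|---|---|
| 0.3 SD | 1.98 | 29% | 16% | 12% |
| 0.5 SD | 5.34 | 64% | 39% | 29% |
| 0.8 SD | 12.77 | 95% | 80% | 67% |

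The test therefore misses a 0.5 SD difference 36–71% of the time and a 0.3 SD difference 71–88% of the time.

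**3. Simulation of the rule.** Settings: 118 participants, 25% missing, five baseline variables, 800 runs per scenario, true effect 0.7 SD, assumed baseline–outcome correlation 0.3 or 0.5. Slopes are log-odds of dropout per SD.

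| Dropout depends on | Slope | Little's test rejects | Complete-case bias (SD) |
|---|---|---|---|
| nothing (MCAR) | – | 5% | about 0 |
| baseline score | 0.5 | 34% | about 0 |
| baseline score | 1.0 | 91–92% | about 0 |
| unseen 3-month score, both arms | 0.5–1.0 | 6–27% | −0.01 to −0.09 |
| unseen 3-month score, intervention arm only | 0.5–1.5 | 5–16% | +0.09 to +0.29 |

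In the last row the bias was the same in runs that passed Little's test, so passing gives no reassurance. In points, at the protocol's SD of 2.86: 0.09 × 2.86 = 0.26 and 0.29 × 2.86 = 0.83.

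**4. Does MAR imputation remove that bias?** No. Imputing the outcome from the covariates already in the analysis model adds no information. With intervention-arm dropout at slope 1.0, SD 2.86 and a true effect of 2.0 points, complete case and MAR-based MI were both biased by +0.52 points at correlation 0.5 and by +0.59 at 0.3. At slope 0.5 both were biased by +0.27. If half of the 3-month dropouts returned at 6 months and that score entered the imputation, the MI bias at slope 1.0 was still +0.39 to +0.44.

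**5. The completer versus non-completer tests.** At least one of five t-tests was significant in 19–20% of runs under true MCAR, in 65–70% when dropout depended on baseline at slope 0.5, and in 22–63% when it depended on the unseen score. With ten independent tests under MCAR the figure is 1 − 0.95¹⁰ = 40%. A significant result does not separate MAR from MNAR. The SAP also does not say which pattern of results would count as suggesting MAR.

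**The case against.** **Adjustment already protects the estimate.** The primary model (SAP 6.6) adjusts for baseline BGSI attainment, gender, age, years of education and baseline RBANS. Where dropout depends only on these, complete case is unbiased, as the simulation shows. This stands. It means that a missed departure from MCAR is often harmless; it does not make the test a sound basis for choosing the analysis.

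**Little's test is not blind.** A reader might infer that it almost never finds a problem at this sample size. The figures do not support that: it detects a 0.8 SD difference 67–95% of the time. It is weak for smaller differences and for outcome-dependent dropout.

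**The bias under MNAR is not the price of this rule.** A reader might take the half-point bias as the harm that switching to imputation would undo. Step 4 shows that it would not. MI gains over complete case only through information outside the primary model, such as the 6-month score or other predictors of dropout.

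**The t-tests and chi-square tests do not choose between complete case and imputation.** Both of their branches impute. The second allows for non-MAR modelling, but does not define it and is reached only if Little's test rejects.

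**ITT and precedence.** SAP section 4 states a principle, and analysing observed outcomes as randomised is often called ITT, so a flat contradiction would be too strong a claim; the two sit poorly together. Protocol section 6 leaves the planned analysis to the SAP. But it names imputation with a complete-case comparison, and protocol v1.13 (20/12/2024) still says so after SAP version 1 (05/09/2024).

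**25% is a planning allowance.** The loss of about 30 participants depends on it.

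**Conclusion.** Wrong as written; it should be fixed. Three defects need no simulation. A non-significant Little's test is read as showing MCAR and sets the primary analysis. Tests on observed variables are asked to establish MAR, which they cannot do. The rule conflicts with protocol section 6.

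A fourth is a gap: if complete case becomes primary, no missing-data sensitivity analysis follows, and neither route requires a defined MNAR analysis.

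The size depends on assumptions that the documents do not settle: a 5% level for Little's test, 1 to 10 variables in it, one dropout pattern, correlations of 0.3 to 0.5, and the dropout slopes. On these, power runs from 12% to 95% for differences of 0.3 to 0.8 SD, and rejection under outcome-dependent dropout is 5–27%. The bias of +0.09 to +0.29 SD under intervention-arm MNAR dropout is the reason for an MNAR analysis; it does not measure what this rule costs relative to MAR-based imputation.

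**What to change.** - Delete the MCAR/MAR test sequence as a means of choosing the analysis. Baseline comparisons of completers and non-completers can stay as description.
- Pre-specify one primary approach for all randomised participants: MI under MAR, as in the protocol, or a likelihood repeated-measures model of the 3- and 6-month scores with baseline as covariate.
- Always report complete case as a sensitivity analysis.
- Add a delta-adjusted MI analysis of the 3-month BGSI. Lower the imputed intervention-arm scores by 0.5, 1, 1.5 and 2 points and report the value at which the conclusion changes. With 25% of that arm missing, the largest step moves the arm mean by 0.25 × 2 = 0.5 points.

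The cost is SAP wording and a few extra imputation runs, with no new data. The change also brings the SAP into line with the protocol. If the analysis has already been run, record the change as a justified deviation, as protocol section 6 requires.

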### 7.1 Power calculation

Evidence from the GREAT trial of cognitive rehabilitation in neurodegenerative disease using the same primary outcome Bangor Goal Setting Interview (BGSi) indicated an effect of approximately 0.8 in a population with dementia. This is likely to be an underestimation of the effect in this study as it is likely that the intervention will be more effective in people without neurodegeneration as seen in the population in the GREAT trial.

Assuming a minimally clinically important difference of 2 points (<https://www.thecopm.ca/faq/>) and a more conservative effect of 0.7 would require SD of the measure to be approximately 2.86. Baseline SD observed in the GREAT trial was 1.74, it is likely that variability in our sample is likely to be larger and therefore we can accommodate an Increase in variability of approximately 65%.

A sample of 88 (44:44) will be required to detect an effect of 0.7 on the BGSi at 3 months with 90% power at a 5% significance level. Incorporating an attrition of 25% will require recruitment and randomisation of 118 participants (59:59).

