### **4.2 RANDOMISATION**

Randomisation will take place once consent and baseline data collection has been completed. Randomisation will be on a 1:1 allocation (intervention:control) via a secure online system hosted by NWOORTH, Bangor University. The system will employ a dynamic adaptive randomisation algorithm. The randomisation will be stratified for centre (London/Sussex/Southampton/Manchester). A member of the research team at UCL will enter the participants details into the web form and perform the randomisation, which will either display directly on screen, if the researcher is unblinded or notification of the randomisation result will be sent to the designated parties to organise ongoing contact.

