## 6.6 ANALYSIS OF PRIMARY OUTCOME

The primary outcome, the BGSi (attainment score) at the 3 months, will be analysed using a multi-level (mixed effect) linear regression model to assess the differences between the two treatment arms. Stratification variables (Site) will be incorporated into the model as a random effect along with gender, age (continuous), years of education (continuous) and RBANS composite score at baseline as fixed factors. Baseline BGSi attainment score will also be incorporated to account for any differences at baseline.

The BGSi at 6 months will be analysed as a secondary outcome using the same model structure as the primary. Unadjusted (section 6.5) and adjusted results will be presented with associated 95% confidence intervals.

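### The imputation model in SAP 4.6 need not contain the covariates of the primary analysis model, baseline BGSI above all, so multiple imputation can be less precise than complete-case analysis and is biased if baseline-related dropout differs between arms

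*Combined protocol and SAP*

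**What the plan says.** **Imputation model (SAP 4.6).** Missing outcomes are to be "imputed using Allocation Group and Stratification factors (Site) and other variables that are deemed to be predictors of missingness". A variable counts as a predictor of missingness if a test finds a difference between completers and non-completers. The candidates are introduced by "Variables to be assessed as predictors of missingness include" and are age, sex, ethnicity, education, disability, occupation, drugs, CV19 conditions, number of vaccines and cognition. Association with the outcome is not a criterion for entry.

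**Analysis model (SAP 6.6).** BGSI attainment at 3 months is regressed on allocation, with site as a random effect and gender, age, years of education and baseline RBANS as fixed effects. In addition, "Baseline BGSi attainment score will also be incorporated to account for any differences at baseline". SAP 6.7 gives the secondary outcomes the same structure, each with its own baseline score.

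**When imputation applies (SAP 4.6).** Below 5% missing, or if Little's test indicates MCAR, complete cases are analysed. Above 40% missing there is no imputation. Between these limits, if MCAR is rejected and further tests suggest MAR, predictive mean matching is used. SAP 4.6 and 6.9 then add a complete-case sensitivity analysis of the primary outcome.

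The protocol's section on statistical analysis names multiple imputation but lists no variables, so it does not fill the gap.

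**The concern.** Only allocation and site are certain to be in both models. An imputation model without baseline BGSI draws a missing 3-month score as if it were unrelated to the participant's starting score. This has two consequences.

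- **Precision.** The imputed share of the data carries no baseline relation. The fitted baseline slope is therefore diluted, by about 25% when 25% is imputed, and part of the gain from covariate adjustment is lost.
- **Bias.** Each arm's imputed values are centred on that arm's completers. If completers in the two arms differ in baseline score because dropout worked differently, the difference passes into the treatment effect.

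At stake is the primary estimate in the situation the rule is written for, where missingness already appears related to observed data. Participants are not blinded, and one arm has ten sessions while the other has usual care. Dropout that differs by arm is therefore plausible, although the documents give no figures on it.

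**Working it through.** **Inputs from the documents**
- Test level (SAP 4.3): "All statistical tests will be two-sided and performed using 5% level of significance".
- Size (SAP 4.1): "A sample of 88 (44:44) will be required to detect an effect of 0.7", with 90% power; then "Incorporating an attrition of 25% will require recruitment and randomisation of 118 participants (59:59").
- Allocation (SAP 4.2): "Randomisation will be on a 1:1 allocation (intervention:control").
- Scale (protocol, Power calculation): with a 2-point difference, "a more conservative effect of 0.7 would require SD of the measure to be approximately 2.86".

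**The plan's own figures reproduce.** A two-sample noncentral-t calculation with effect 0.7, two-sided 5% and 44 per arm gives power 0.901. Then 88 / 0.75 = 117.3, which rounds up to 118 for equal arms. And 2 / 0.7 = 2.857.

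**Simulation.** 118 were randomised 1:1, with about 25% of 3-month outcomes missing and a true effect of 0.7 SD. Imputation was by predictive mean matching (5 donors, 25 imputations, Rubin's rules), with 1,000–1,500 replicates per scenario. The analysis model was treatment, baseline and site, with three sites as fixed indicators and the other covariates omitted. The baseline-to-3-month correlation r is not in the documents and is assumed at 0.3, 0.5 and 0.7. The dropout patterns are also assumptions.

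*Power when both arms behave alike*

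| Dropout | r | MI without baseline | MI with baseline | Complete case | Loss, without vs with (points) |
|---|---|---|---|---|---|
| Unrelated to baseline | 0.3 | 0.885 | 0.909 | 0.919 | 2.4 |
| | 0.5 | 0.918 | 0.959 | 0.965 | 4.1 |
| | 0.7 | 0.942 | 0.994 | 0.997 | 5.2 |
| Related, same in both arms | 0.3 | 0.863 | 0.871 | 0.895 | 0.8 |
| | 0.5 | 0.903 | 0.942 | 0.949 | 3.9 |
| | 0.7 | 0.944 | 0.984 | 0.987 | 4.0 |

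These runs give a loss of about 1–5 points; over all the runs made, the span is roughly 1–8. At r = 0.5 with dropout unrelated to baseline, the mean standard error is 0.203 without baseline, 0.186 with it and 0.188 for complete cases. Since (0.188/0.203)² = 0.858, imputing without baseline is like analysing 0.858 × 88 ≈ 75 completers instead of 88. When both arms behave alike, the bias without baseline is at most about 0.03 SD.

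*Bias when the arms differ.* If imputed values centre on each arm's completers, then approximately

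bias ≈ r × (mean baseline of intervention completers − mean baseline of control completers), in SD units.

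| Dropout related to baseline | r | Bias without baseline | Bias with baseline | Implied gap (bias / r) | 95% CI coverage without baseline |
|---|---|---|---|---|---|
| One arm only | 0.3 | 0.044 | −0.014 | 0.15 | 0.938 |
| | 0.5 | 0.085 | −0.015 | 0.17 | 0.925 |
| | 0.7 | 0.146 | −0.004 | 0.21 | 0.886 |
| Opposite directions | 0.3 | 0.125 | 0.006 | 0.42 | 0.915 |
| | 0.5 | 0.204 | −0.004 | 0.41 | 0.836 |
| | 0.7 | 0.300 | 0.001 | 0.43 | 0.654 |

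Under no effect, at r = 0.5, the type I error without baseline is 0.056 for one-arm dropout. For opposite-direction dropout it is 0.153, against 0.055 with baseline included.

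A second mechanism, with a logit slope of 1.2 per SD acting the other way, gives biases of −0.16 SD (one arm) and −0.26 SD (opposite) at r = 0.5. Including baseline leaves about −0.04. Across both mechanisms and all r, the size of the bias is 0.04–0.22 SD for one arm and 0.13–0.38 SD for opposite directions. The sign depends on which participants leave which arm. At an SD of 2.86 points these ranges are 0.04 × 2.86 = 0.11 to 0.22 × 2.86 = 0.63 points, and 0.13 × 2.86 = 0.37 to 0.38 × 2.86 = 1.09 points.

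**Would the completer test bring baseline in?** Suppose baseline BGSI were tested at p < 0.05, pooling the arms. It is flagged in over 99% of trials if both arms behave alike at slope 1.2. With one-arm dropout it is flagged in about 61% at slope 1.2 and 39% at slope 0.8. With opposite-direction dropout it is flagged in only 3–5%, because the arms cancel. At slope 1.2 and r = 0.5 the biases are:

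| Dropout | Omitted | Test-gated | Always in | Complete case |
|---|---|---|---|---|
| One arm | −0.15 | −0.08 | −0.04 | −0.01 |
| Opposite | −0.26 | −0.25 | −0.05 | −0.01 |

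**The case against.** Four points can be made for the plan.

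1. *The candidate list is open.* The wording that introduces it does not exclude baseline BGSI, so a reader who infers that the SAP forbids the variable goes too far. This stands, but helps only in part. Baseline is unnamed, and the pooled test that would admit it works least well where the arms differ, which is where the omission does harm.

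2. *Imputation is conditional.* A reader might infer that the trial loses this power whenever data are missing. The SAP does not support that: data judged MCAR go to complete cases. The rows above for dropout unrelated to baseline apply only where imputation is reached because missingness depends on something else, or because Little's test rejects by chance. At the plan's own effect the loss is also modest: power without baseline stays at 0.86–0.94 in the table above.

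3. *Bias is not inevitable.* It is negligible when dropout depends on baseline in the same way in both arms. Its size rests on an assumed correlation and dropout pattern, and the documents do not show how strongly baseline BGSI predicts the 3-month score. This stands in full.

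4. *A safeguard exists.* Complete-case analysis of the primary outcome is required whenever imputation is used, and it was essentially unbiased in these scenarios. A distortion could therefore be seen. However, the SAP has no rule for choosing between the two results if they disagree.

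**Conclusion.** The mismatch is real, and nothing else in the documents repairs it: the imputation model may omit baseline BGSI and any of the other fixed covariates of the primary model. When imputation is triggered, the result can be less precise than the complete-case analysis it replaces, by roughly 1–8 power points at 0.7 SD with 25% missing and r of 0.3–0.7. Bias of 0.04–0.22 SD (one arm) or 0.13–0.38 SD (opposite directions) arises only if baseline-related dropout differs by arm.

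The documents do not support the stronger conclusion that the primary result will be biased or the trial underpowered. The correlation and the dropout mechanisms are assumptions, and the simulation simplifies the site term and leaves out the other covariates. The point is best treated as a free improvement to the SAP.

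**What to change.** Replace the sentence on imputation variables in SAP 4.6 with a rule of this kind: the imputation model for each outcome always contains every variable in its analysis model (allocation, site, baseline score of the outcome, gender, age, years of education, baseline RBANS) and the same outcome at the other follow-up visit, plus auxiliary variables that predict missingness or the outcome. Completer/non-completer tests may help choose auxiliary variables but should not decide whether analysis-model variables enter.

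It would also help to state in SAP 6.9 how a disagreement between the imputed and complete-case results will be interpreted.

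The cost is SAP wording and a slightly larger imputation model. All the variables are already collected, and baseline data are completed before randomisation. If analysis has begun, document the change and report the results under both imputation models.
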